## Abstract

**Background:** Rising obesity rates among young adults increase long-term health risks, especially cardiometabolic conditions such as type 2 diabetes mellitus. Digital interventions can offer scalable solutions to promote and support healthy behaviors by integrating personalized diet, physical activity promotion, and behavioral support. **Objective:** To assess the feasibility, user friendliness, adherence, and satisfaction of the Healthy Lifestyle Recommender System (HLRS). Secondary outcomes will include measures of metabolic health and obesity. **Methods:** A 3-month, single-arm pilot study conducted across European countries, including Bulgaria, Germany, Italy, Netherlands, Portugal, and Spain, enrolling 351 young adults (18–25 years old, BMI 18.5–29.9 kg/m^2^). The intervention includes a mobile app for meal planning (Nutrida v.1), gamified physical activity encouragement (GameBus), and real-time monitoring via a wearable smartwatch device. Primary outcomes are adherence and engagement, measured through app usage and participant feedback; secondary outcomes include anthropometry, physical activity, dietary patterns, psychological well-being, and selected biomarkers of metabolic health. **Expected Outcomes:** Improved engagement is expected to enhance lifestyle behaviors, supporting weight management and overall well-being. Findings will guide future large-scale interventions. **Conclusions:** This study will contribute to minimizing the impact of obesity in Europe.

## 1. Introduction

Young adulthood, often defined as ages 18–24 [1], represents a crucial life stage marked by increased independence, lifestyle transitions, and the establishment of long-term health behaviors. Many young adults leave their family homes to pursue education or start professional careers, which brings environmental changes and makes this age critical for weight control [2]. However, this period is also associated with a higher risk of adopting unhealthy dietary habits, reduced physical activity, and increased sedentary behaviors, contributing to weight gain and metabolic health risks [3,4,5,6,7]. In 2022, one in eight people worldwide were living with obesity; adult obesity has more than doubled since 1990. Of 2.5 billion adults aged 18 or older (43% of adults), 890 million were living with obesity (16% of the population). Given the rising obesity rates in this population [8], early and tailored interventions are essential to prevent long-term health consequences [9].

Traditional weight management strategies, such as prescribed weight-loss diets or physical activity [10,11] often fail to engage young adults due to their structured and rigid nature, as well as common barriers such as time constraints, financial limitations, and a preference for convenience over nutritional quality [12,13]. Digital health technologies, including mobile applications and wearable devices, offer a promising alternative by providing flexible, interactive, and personalized approaches to health promotion [14,15,16].

The widespread integration of technology into daily life has positioned digital health tools as a promising approach for promoting healthy behaviors and preventing chronic diseases. This is particularly relevant for young adults, who have grown up in a digital environment and are highly accustomed to using mobile applications and wearable devices. Studies have shown that adherence to digital health interventions is generally higher in young adults compared to older populations, likely due to greater technological literacy and engagement [17,18].

The HealthyW8 project, a pan-European initiative funded by the EU Horizon Calls, addresses these challenges by implementing a Healthy Lifestyle Recommender Solution (HLRS) by means of a digital platform using mobile applications. The novelty of the HealthyW8 project is its approach to weight gain through personalized and holistic recommendations, integrating key lifestyle factors such as dietary patterns, physical activity, sleep, psychological and behavioral aspects, and emotional well-being, and using behavioral nudging, gamification, and real-time feedback to enhance user engagement and adherence. Additionally, the system will use a Human Digital Twin (HDT) model, which collects data from wearable devices, self-reported inputs, and app interactions to anticipate barriers and tailor recommendations dynamically (https://www.healthyw8.eu/ accessed 21 October 2025).

Building on this evidence, the current study will evaluate the feasibility, adherence, and user satisfaction of the digital HLRS among young adults in the participating consortium countries, recognizing this life stage as pivotal for establishing lasting health behaviors. The findings will provide valuable insights to optimize digital interventions for obesity prevention in this demographic, ensuring their relevance and long-term effectiveness.

## 2. Methods

### 2.1. Study Design

This study is a prospective, multi-center, single-arm, non-controlled 3-month pilot trial conducted across several European locations including Bulgaria, Germany, Italy, Netherlands, Portugal, and Spain. It is designed as a preliminary three-month intervention (pre-post design) to test the feasibility and effectiveness of a mobile health application, with the goal of laying the foundation for a future 12-month longitudinal study with an intervention group (app) and a control group (standard recommendations). The current study design will be consistent across countries, with minor adaptations to account for local contexts. NCT07011368 is the registration number for this study on ClinicalTrials.gov (https://clinicaltrials.gov/study/NCT07011368 (accessed on 8 July 2025)).

### 2.2. Population: Inclusion and Exclusion Criteria

The pilot trial usually involves 30 young adults of both sexes per country; however, the final number of participants depends on each country, and there are a total of approximately 351 participants (Table 1). Inclusion criteria are age of 18–25 years, residence in the regions where the trials are conducted, BMI between 18.5 and 29.9 kg/m^2^ (normal weight to overweight), willingness to participate, ownership of a smartphone, and basic mobile application skills.

Exclusion criteria include individuals with obesity (BMI > 30.0 kg/m^2^), chronic conditions such as cancer, Parkinson’s disease, or other illnesses requiring specific treatments or significantly affecting normal physiology (e.g., metabolic disorders), cognitive impairments (e.g., Alzheimer’s disease), inability to live independently, adherence to specific diets, or inability to provide voluntary informed consent. However, individuals being treated for conditions such as type 2 diabetes, hypertension, or elevated blood lipids (e.g., triglycerides, cholesterol) will be included to ensure the recruitment reflects the typical demographic. If the drop-out or discontinuation rate exceeds 10%, additional participants will be recruited to maintain a minimum sample size of 20 participants per study site.

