## 3. Statistics

Sample Size Calculation: The study hypothesizes that the use of HLRS (≥45 min per week) will not decrease by more than 20% over the 3-month intervention period. Assuming a 30% standard deviation in usage, a 0.05 significance level, and 80% power, 20 participants would be required for a paired design. To compensate for an expected 33% attrition, 30 participants will be recruited, ensuring sufficient power. An equal distribution of males and females will be targeted to enhance the generalizability of the findings.

Handling of Missing Data and Dropout: No imputation will be performed for missing data. Participants who withdraw will be excluded from further analysis beyond their last available data. In order to maintain sample size and statistical power, replacements will be made as necessary, ensuring at least 20 participants complete the study. This method safeguards the integrity of the data and minimizes potential bias.

Data Analysis: Normality of the data will be assessed through Q-Q plots and Kolmogorov–Smirnov tests. Non-normally distributed data will be analyzed using non-parametric methods such as the Friedman test, followed by pairwise comparisons, and log transformations if appropriate. A significant level of *p* < 0.05 will be considered. Data will be analyzed using SPSS (version 25.0) and R (version 4.4.1). Since outcomes will be mainly descriptive, simple and descriptive statistics will summarize baseline participant characteristics, and changes over time will be assessed using paired t-tests, to evaluate the impact of the intervention on health outcomes.

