## Figures and Tables

**Figure 1 jpm-15-00625-f001:**
[figure not shown]
Flow-chart of the trial design and data and sample collection.

**Table 1 jpm-15-00625-t001:** Recruitment strategies in countries participating in the HealthyW8 young adults’ trials.

Country, Partner	Number of Participants Targeted for Enrollment	Number of Participants Required for Study Conclusion	Recruitment Strategies	Coordinating Entity	Medical Principal Investigator
Bulgaria, RCNE	30	20	Using the network of the Regional Cluster North-East, word-of-mouth	RCNE	No
Germany, BIPS/DFKI	30	15	Word-of-mouth, flyer, press release, Instagram	BIPS	No
Italy	101	52	Flyers, word-of-mouth, conferences, social media, institutional website, local press	USG	A medical nutritionist involved in the screening
Netherlands	40	20	Flyers and posters, institutional website and newsletter, social media, word-of-mouth	TU/e	No
Portugal	30	15	Flyers, word-of-mouth, conferences, social media, institutional website, local press	CIAS, UC	No
Portugal	30	15	Flyers, word-of-mouth, conferences, social media, institutional website, local press	UEV	No
Spain	60	25	Flyers, word-of-mouth, conferences, social media, institutional website, local press	CITA	No
Spain	30	20	Word-of-mouth, newspaper advertisement, flyers, physicians, and other healthcare professionals.	IDISBA	Yes

Abbreviations: RCNE: Regional Cluster North-East; BIPS GmbH/Deutsches Forschungzentrum fur Kunstliche Intelligenz GmbH; CIAS, UC: Research Center for Anthropology and Health of the Universidade de Coimbra; CITA: Agro-food Technological Center of Aragon; USG: Universitá Degli Studi di Scienze Gastronomiche; TU/e: Eindhoven University of Technology; UEV: Universidade de Évora; CITA: Centro de Investigación y Tecnología Agroalimentaria de Aragón; IDISBA: Foundation of Institute of Health Research of the Balearic Islands.

**Table 2 jpm-15-00625-t002:** Features included in the intervention through the HLRS.

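### Table 1 lets three sites conclude with 15 participants, against a minimum of 20 per site in section 2.2 and the 20 behind the 80% power in section 3

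*Protocol article*

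**What the plan says.** Three places in the protocol article fix how many participants must remain.

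- **Section 2.2** makes replacement conditional on drop-out above 10% and gives its purpose: "additional participants will be recruited to maintain a minimum sample size of 20 participants per study site". The unit is the study site.
- **Section 3, sample size paragraph**: "Assuming a 30% standard deviation in usage, a 0.05 significance level, and 80% power, 20 participants would be required for a paired design". It continues: "To compensate for an expected 33% attrition, 30 participants will be recruited, ensuring sufficient power". The missing-data paragraph repeats the floor, with replacements "ensuring at least 20 participants complete the study". Neither paragraph says whether the 20 is per site, per country or for the trial.
- **Table 1** has a column headed "Number of Participants Required for Study Conclusion". It reads 15 for Germany (BIPS/DFKI), Portugal (CIAS, UC) and Portugal (UEV), each with 30 targeted for enrolment. The other five sites read 20, 52, 20, 25 and 20.

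**The concern.** A site cannot have both a minimum of 20 kept up by replacement and a conclusion requirement of 15. The 20 in section 2.2 has to mean participants remaining, because it is maintained by replacing those who leave. It is therefore the same kind of number as the Table 1 column.

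Two things are at stake. The first is operational: at 15 completers, a coordinator at one of the three sites would recruit more under section 2.2 and could close under Table 1. The second is the power statement. Section 3 ties 80% power to 20 completers. If that is meant for each site, it is not delivered where 15 is accepted. If it is meant for the whole trial, it gives no support to the per-site minimum.

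**Working it through.** **Inputs**

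- Change: 20 percentage points, from the hypothesis that usage "will not decrease by more than 20% over the 3-month intervention period" (section 3).
- SD: 30% (section 3), taken here as the SD of the within-person change. The article does not say which SD it means.
- Significance level 0.05, power 80%, paired design (section 3). Sidedness is not stated.
- Attrition 33%, 30 recruited (section 3).
- Enrolled and required numbers by site (Table 1).

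**Step 1: reproduce the plan's 20 and 30**

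Normal approximation: n = ((z for alpha + z for power) × SD / change)².

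- Two-sided: ((1.960 + 0.842) × 30/20)² = 17.66, so 18.
- One-sided: ((1.645 + 0.842) × 30/20)² = 13.9, so 14.

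Exact paired t test (noncentral t, n − 1 degrees of freedom, noncentrality (20/30) × √n): the smallest n with power of at least 80% is

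- two-sided: n = 20, power 80.7%;
- one-sided: n = 16, power 81.6%.

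Of these four versions, only the two-sided t test gives the plan's 20. Inflation for drop-out: 20 / (1 − 0.33) = 29.9, so 30. Both stated figures are reproduced; the calculation itself is not at fault.

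**Step 2: power at the Table 1 figure of 15**

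| Version | n = 15 | n = 20 |
|---|---|---|
| Two-sided t (reproduces 20) | 67.1% | 80.7% |
| One-sided t | 79.1% | 89.0% |
| Two-sided normal | 73.3% | 84.6% |
| One-sided normal | 82.6% | 90.9% |

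Only the one-sided normal approximation keeps 15 above 80%, and that version would have asked for 14, not 20. With the two-sided t test, the change detectable with 80% power at 15 completers is about 23.3 points instead of 20.

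**Step 3: the replacement rule at a site with 15 left**

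Loss is 1 − 15/30 = 50%. This is above 10%, so the rule in section 2.2 is in force, and the site is 20 − 15 = 5 below its minimum. Table 1 treats the same site as complete.

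**Step 4: the two readings of the unit**

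- *Per site.* The pair 30 and 20 in section 3 matches the usual 30 per country and the 20 per site in section 2.2. On this reading the stated power fails at the three sites (Step 2).
- *Whole trial.* Twenty completers would suffice for the trial, and Table 1 requires 20 + 15 + 52 + 20 + 15 + 15 + 25 + 20 = 182. The three entries of 15 then do not threaten power, but the minimum of 20 per site has no source in the calculation.

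Neither reading makes the three places agree.

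**Step 5: enrolment needed for 20 completers**

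At 33% attrition: 30, as planned. At 50% loss, which is what 15 of 30 would allow: 20 / 0.5 = 40.

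**The case against.** The strongest reply is that 67% power has no planned analysis to attach to. Section 3 nowhere announces a test within each site and calls the outcomes mainly descriptive. This stands, and it is why the power figure is given here only for the per-site reading. It does not remove the clash between 15 and 20, which involves no power argument.

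A second reply is that section 2.2 lets final numbers vary by country. That allows different enrolment totals. It does not waive the floor per site set at the end of the same section.

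Three stronger criticisms are tempting, and the documents do not support them.

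- *Table 1 contradicts the 33% attrition.* The columns sum to 351 enrolled and 182 required, and a reader might infer 48% attrition (1 − 182/351). But the column gives floors, while the 33% is an expectation. At 33%, 351 × 0.67 leaves about 235, above 182. A floor below the expected yield contradicts nothing, and the five other sites all meet 20.
- *The 10% trigger is a rival attrition assumption.* It is a condition for topping up to 20. A site of 30 that loses a third passes the trigger and still holds 20. The wording is loose, but it does not conflict with 33%.
- *The trial's real precision is that of 182 pooled completers.* Table 3 gives an intervention of 1.5 months in Italy and 1 to 2 months in the Netherlands. Those sites supply 52 + 20 = 72 of the 182, so a pooled 3-month figure cannot be read off that total.

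**Conclusion.** The point holds as an inconsistency. Three of eight sites have a conclusion requirement of 15 against a stated minimum of 20 per site, and the unit of the 20 in section 3 is undefined. On the per-site reading, power at those sites is about 67% rather than 80%. That rests on a 20-point change, an SD of change of 30 and a two-sided 0.05 paired t test, the last being an inference from its reproducing n = 20; a one-sided t test gives about 79%. On the whole-trial reading there is no loss of power, but the per-site minimum cannot be presented as a result of the calculation.

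It should be fixed. In a single-arm, mainly descriptive pilot it does not undermine the study as a whole, but it leaves replacement and site closure governed by two different numbers.

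**What to change.** Make sections 2.2 and 3 and Table 1 agree, in one of two ways.

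1. **Keep 20.** Change the three Table 1 entries from 15 to 20. At the plan's own 33% attrition the enrolment target of 30 stays. If the sponsor in fact expects 50% loss at these sites, the target there becomes 40, which is 10 more at each of three sites.
2. **Keep 15.** Remove the minimum of 20 per site from section 2.2 and state that the 80% power does not apply to single-site tests at these three sites.

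In either case, add one sentence to section 3 naming the unit (site or trial) to which the 20 and the 80% power refer, and state the sidedness of the test.

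The cost is an edit to three places. The second option adds no recruitment but gives up a favourable statement. The first adds recruitment only if losses above 33% are expected or occur.

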### 2.3. Participants’ Involvement

Participants who meet the inclusion criteria will be involved in setting the research question and in the design and implementation of the intervention and outcome measures. Participants will also play a central role in disseminating baseline information, which helps to motivate community involvement during and beyond the study.

### 2.4. Recruitment

Recruitment is scheduled to begin in the last semester of 2025. Strategies and specific details for each country are outlined in Table 1. Potential participants can register by phone, email, or postal mail, as well as through universities, social media campaigns, and healthcare facilities. Recruitment strategies will be adapted per country to ensure cultural and contextual relevance. Interested individuals will complete an online screening questionnaire to determine eligibility. Study personnel will organize an enrollment session to provide a brief overview of the study, distribute the participant information sheet, and obtain informed consent from each participant.

### 2.5. Intervention

The intervention was developed collaboratively by the HealthyW8 consortium and global healthcare professionals to meet the unique needs of young adults. It offers personalized features that enable participants to tailor their dietary and physical activity choices based on preferences, budget, allergies, and physical capabilities. Central to the intervention is the HLRS, which included features shown in Table 2.

Optional access to the Open Stakeholders Platform (OSP) for supplementary information and knowledge exchange among stakeholders in obesity prevention will be found at https://www.stakeholders.healthyw8.eu/.

Table 3 provides an overview of the specific tools and equipment used in each participating country for the pilot study. All tools for data and sample collection and analysis, as well as for shipping these samples to the laboratories that will analyze them (LIH and IDISBA), were previously defined and harmonized, ensuring methodological consistency while allowing for country-specific adaptations.

### 2.6. Follow-Up and Data Collection

The study spans 90 days (3 months) and is structured into five phases: enrollment (Dx), baseline visit (Day 0), and final visit (Day 90) in most of the participating partners. Data collection occurs at baseline and final visits, with regular check-ins via phone calls, or in-person meetings to maintain engagement. Figure 1 summarizes the timeline and interventions at each stage. Each study phase (outlined in Table 4) is described as follows:Enrollment visit (Dx): Informed consent (after receiving written and verbal information about the study’s objectives, risks, and benefits), eligibility assessment (assessed based on anthropometric measurements, and screening questionnaires on general health and lifestyle), and meeting inclusion criteria.Baseline visit (Day 0): Anthropometric data, baseline questionnaires, biological samples (blood, urine, and saliva, where applicable), and instructions on using the HLRS platform. Recommendations will be adapted to the previously diagnosed health status, A1c levels or blood pressure of the participant. Participants will receive instructions on using the HLRS platform.Final visit (Day 90): Repeat assessments and questionnaires to evaluate changes over the study.

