### 2.7. Outcome Measures and Data Collection

Primary outcomes focus on adherence and user experience, measured by app usage frequency/duration and wearable device data. User experience is evaluated using validated tools such as the User Experience Questionnaire [20,21].

Secondary outcomes include anthropometric measures, biological markers, physical activity, and dietary patterns, assessed through wearables and validated questionnaires, as described below and summarized in Table 4.

Anthropometric measurements: Body weight, height, waist circumference, hip and thigh circumferences will be taken, and body composition will be conducted following standardized procedures, with specific equipment varying by country. Body weight will be recorded with participants wearing light clothing and no shoes. A predetermined weight will be subtracted to account for clothing. Height will be measured to the nearest millimeter with participants standing upright and maintaining the Frankfurt Horizontal Plane. Body mass index (BMI) will be calculated as weight (kg) divided by the square of height (m^2^). Waist circumference (WC) and hip circumference (HC) will be measured in duplicate using an anthropometric tape, ensuring proper positioning and participant posture. WC will be assessed at the midpoint between the lowest rib and the iliac crest, while HC will be measured at the widest part of the hips, with the tape placed horizontally around the body. Participants will stand upright with feet together, and the average of the two measurements will be recorded for analysis [22].

Biological samples: The participants may provide saliva, urine, and blood samples. Urine samples will be collected the day after completing a 24 h Recall (24hR) to accurately assess dietary biomarkers. Additional assessments, including markers of oxidative stress and inflammation (Table 4), will be performed using commercial ELISA kits according to the manufacturer’s instructions [23,24,25].

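### On the visible schedule only participants who reach the final visit can rate user experience, a primary outcome, so the result describes those who stayed

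*Protocol article*

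**What the plan says.** All references are to the Protocol article.

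- **Outcome.** Section 2.7: "Primary outcomes focus on adherence and user experience, measured by app usage frequency/duration and wearable device data". It continues: "User experience is evaluated using validated tools such as the User Experience Questionnaire". The Abstract also names user friendliness and satisfaction as objectives.
- **Schedule.** Section 2.6: "Data collection occurs at baseline and final visits, with regular check-ins via phone calls, or in-person meetings to maintain engagement". For the last contact: "Final visit (Day 90): Repeat assessments and questionnaires to evaluate changes over the study".
- **First exposure.** Under the baseline visit, section 2.6 says: "Participants will receive instructions on using the HLRS platform".
- **Withdrawal.** Section 3: "No imputation will be performed for missing data" and "Participants who withdraw will be excluded from further analysis beyond their last available data". Leavers are replaced so that at least 20 participants complete. The section presents this approach as one that keeps bias small. Section 2.2 triggers extra recruitment when drop-out passes 10%.
- **Where the UEQ is collected.** Table 4 marks it at every site except Italy and gives no visit or week. Section 2.7 lists it among the REDCap questionnaires, also without a time point.

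**The concern.** A participant cannot rate an app before using it, so the baseline visit yields no user-experience data. Of the two data-collection visits in section 2.6, only the final one remains. The article describes no rating at withdrawal. For most measures, keeping data up to the last available point preserves something from a leaver. For the UEQ there is no earlier point to keep.

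Poor usability is a plausible reason for leaving a study of an app. If leavers would have scored it lower, the reported score is too favourable. It may also miss the usability problems that a pilot should find before the 12-month controlled study announced in section 2.1. Replacing leavers restores the number of raters but not the missing opinions, because the replacements who rate are again those who stayed. An analysis plan can add sensitivity analyses later, but it cannot supply ratings that were never taken.

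**Working it through.** **1. The plan's own attrition figure.** Section 3 assumes a 20% margin, a 30% SD, significance level 0.05 and 80% power in a paired design.
- Standardised effect: 20/30 = 0.667.
- A two-sided paired t-test (sidedness is not stated) needs n = 20, with power 0.807.
- Allowing for attrition: 20/(1 − 0.33) = 29.85, rounded up to 30.

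Both stated figures reproduce. They concern app usage, not the UEQ. Here they supply only the expected loss of 33%.

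**2. The loss that Table 1 tolerates.**
- Enrolment targets: 30 + 30 + 101 + 40 + 30 + 30 + 60 + 30 = 351.
- Required for conclusion: 20 + 15 + 52 + 20 + 15 + 15 + 25 + 20 = 182.
- Tolerated loss: 351 − 182 = 169, and 169/351 = 48.1%.

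Italy (101 enrolled, 52 required) does not collect the UEQ. For the seven sites that do:
- Enrolled: 351 − 101 = 250. Required: 182 − 52 = 130.
- Tolerated loss: 250 − 130 = 120, and 120/250 = 48.0%.
- The range across these sites runs from 10/30 = 33.3% (RCNE, IDISBA) to 35/60 = 58.3% (CITA).

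**3. Effect on the score.** Let p be the proportion without a rating, S the mean among stayers and L the mean that leavers would have given.
- Mean over everyone enrolled: (1 − p)S + pL.
- Reported mean: S.
- Overstatement: S − [(1 − p)S + pL] = p(S − L).

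The documents give no value for S − L, so a range is shown, in scale points:

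| Proportion missing | Gap 0.5 | Gap 1.0 | Gap 1.5 |
|---|---|---|---|
| 33% (section 3) | 0.17 | 0.33 | 0.50 |
| 48% (Table 1, UEQ sites) | 0.24 | 0.48 | 0.72 |
| 58.3% (Table 1, CITA) | 0.29 | 0.58 | 0.87 |

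The same formula works for a percentage satisfied. Assume 80% of stayers are satisfied, against 60%, 40% or 20% of leavers. The overstatement is then 7, 13 or 20 percentage points at 33% missing, and 10, 19 or 29 points at 48%. It is zero if leavers would have rated the app as stayers did.

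**The case against.** The strongest reply is that the UEQ's timing is inferred. No passage assigns it a visit, Table 4 is organised by site and not by time, and Figure 1, which summarises the timeline, is not shown. Nor is the schedule sentence a complete list. The same paragraph announces five phases but names three, the 24 h recall is done three times, and app and wearable data accrue between visits. A REDCap form need not be tied to a visit. An article also commonly leaves withdrawal procedures to the full protocol.

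This stands as a limit on certainty: a reader might conclude that the plan rules out an interim or exit UEQ, and the documents do not show that. The point still survives, because the article does state a schedule, a rule for withdrawals and a claim about bias. Followed as written, these leave early leavers unrated. Where the article plans repeated completion, as for the 24 h recall, it says so, and it does not for the UEQ.

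Other stronger readings also go beyond the text:
- **Check-ins serve engagement alone.** The article gives engagement as their purpose but does not exclude other uses.
- **Everyone who stops using the app goes unrated.** Someone who stops using it but attends the final visit can still complete the UEQ. The gap concerns people who leave the study.
- **Nothing is learned from leavers.** Usage logs record their use up to departure, so disengagement shows in the adherence part of the primary outcome. The Abstract also mentions participant feedback. Logs show when use fell, not how the app was judged.
- **48% will be missing.** Table 1 gives minimum numbers to conclude, so 48% is a tolerated loss. The stated expectation is 33%.

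**Conclusion.** The point holds, subject to the inferred timing of the UEQ. On the visible text, the user-experience part of the primary outcome has one usable occasion, and people who leave before it contribute nothing. The result therefore describes completers, and for this outcome the section 3 statement about bias is not supported. Replacement does not change that.

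The share without a rating is 33% if attrition is as planned, and up to 48% (120 of 250) if the UEQ sites finish with only their Table 1 minimums. The overstatement is 0.33 to 0.48 points for each point by which leavers would have scored lower. Its direction and size both rest on an assumed gap. If the full protocol already schedules a UEQ at withdrawal, one sentence in section 2.6 settles the collection issue, and only the reporting changes remain.

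**What to change.** - **Section 2.6:** state when the UEQ is completed. Send the existing form through REDCap when a participant withdraws, with one added item on the main reason for leaving.
- **Section 3:** report UEQ results separately for completers and leavers, with the number enrolled and the number who rated in each group. Describe the final-visit score as a completer result, and limit or remove the statement about bias for this outcome.
- **Optional:** a mid-study UEQ sent alongside an existing check-in. A summary based on each participant's last available UEQ should be at most a sensitivity analysis, because it mixes ratings made after different lengths of use.

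**Cost:** one extra REDCap event using a 26-item form already in the study, and no new visit. It is not free of effort: Table 4 does not mark the UEQ as self-applied, and people who have left usually need a reminder. Response from leavers will be incomplete, so some selection will remain, and the picture of user experience will probably be less favourable.
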